### Behavioral response observation checklist

This observation checklist, prepared by Karkada EC
*et al*., is used in this study by obtaining permission from the author to assess the behavioural responses of low-risk primigravid women during the first stage of labor. A behavioural response checklist has three areas of observation, i.e., the behavioural response in between contractions which has 20 items, facial response during a contraction, which contains eight items; behavioural responses during contractions, which includes 20 items; and lastly, physiological parameters, which have two items. Overall, the tool includes 50 items. The study encompasses negative and positive responses (
Karkada, Noronha, & Dsouza, 2010).

### Questionnaire for assessing the childbirth experience, vaginal birth, or cesarean (QACE)

QACE questionnaire is self reporting tool screens for any negative experiences during child birth. It consists of six main thematic categories. These thematic categories are expectations (three items), sensory experiences (two items), perceived control (six items), relationship with caregivers and the midwife (four items), emotions (seven items), and the first moments with the baby (three items). Additional ten and the other three items are to measure causal indicators that potentially influence the childbirth experience. The response format is a 4-point Likert scale, ranging from “Totally”, “In part”, “Not so much”, and “Not at all” (
Carquillat, P. *et al.*, 2017).

### VAS patient satisfaction scale

The researchers modified the VAS into a patient satisfaction scale to assess the satisfaction level of low-risk primigravid women during labor. It is a 10 cm scale with smileys indicating expression of satisfaction, with the scoring: 0 – indicates no satisfaction and score ranging between 1–3 – mild level of satisfaction, 4–7 – moderate level of satisfaction, and 8–10 – high level of satisfaction (
Hayes and Patterson, 1921).

### Validity and reliability of the study tools

The validity (item Content Validity Index (I-CVI) and Scale Content Validity Index (S-CVI/Ave) and reliability (
Table 1) of the study tools were established by giving the tools, along with the criteria checklist, to a panel of nine experts from different fields, such as the women and child health department of physiotherapy, department of statistics, department of Obstetrics and Gynecological Nursing, and experts from OBG department, Kasturba Hospital Manipal to review the study tools. Content validity is established in terms of relevancy, accuracy, and appropriateness. The item Content Validity Index (I-CVI) and Scale Content Validity Index (S-CVI/Ave) of the tools were calculated based on recommendations by
Polit and Beck (2012).

**Table 1. T1:** Results of the testing of the instruments. *I-CVI- Item - content validity index, *S-CVI- Scale level - content validity index.

Instruments	Content validity		Reliability	
	Mean *I-CVI	*S-CVI/Ave	Aspect of reliability	Reliability score
Structured observational record on the outcome of the labor	1	1	Internal consistency	There was absolutely 100% agreement between two raters: r=1
Behavioural response observational checklist	1	1	Internal consistency	Intra class coefficient agreement. r=0.97
Questionnaire for assessing the childbirth experience vaginal birth or caesarean (QACE)	1	1	Internal consistency	Intra class correlation coefficient: r=0.88
VAS satisfaction scale to measure maternal satisfaction	1	1	Stability	Coefficients of stability: r=0.89

### Data entry and storage

The research assistant will do coding and data entry. The primary investigator will review the data entered for any discrepancies such as data entry errors, missing values etc. One of the co-authors will check the data entry errors by randomly selecting data sheets. A separate laptop will be used for the project store data and can be accessed only by the research assistant and primary investigator.

### Data analysis

Statistical analysis will be performed using
SPSS software version 16. The data analysis will be done based on the objectives and hypotheses of the study. We will follow the intention to treat analysis (ITT). The sample characteristics are measured using descriptive statistics. Two independent samples t-test/Mann-Whitney U-test (based on normality of data) will be used to determine the effectiveness of the usage of peanut ball on the maternal outcomes of labor. Associations among the variables will be computed using the Chi-square test (for categorical variables) and two independent samples t-test/Mann-Whitney U-test or one-way ANOVA/Kruskal Wallis test (for continuous variables). A comparison of behavioural response and stress level of low-risk primigravid women among experimental and control groups will be done using repeated measures of ANOVA. A comparison of childbirth experiences will be done using an independent t-test.

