### Sample-size

The expected variations in the research outcome variable determines the sample size for the study;

n=2Z1−α2+Z1−β2σ2/d2
 (where n is the sample size per group,

Z1−α2
= 1.96 at α = 0.05,

$Z_{1-\beta }$
 = 0.84 (power at 80% power), σ = standard deviation of the primary outcome variable stress level of the mother as measured by serum cortisol level = 2.58 μg/dl (
Stjernholm, Nyberg, Cardell, & Höybye, 2016), d = clinically significant difference = 0.55 μg/dl. The sample size, calculated with an anticipatory attrition rate of 10%, is 768.

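### The trial is sized on a two-sample comparison of maternal cortisol, but the planned repeated-measures ANOVA names no tested term and does not assure the stated 80% power

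*Protocol article*

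**What the plan says.** The Sample-size section (Protocol article) uses the formula for two independent means, "where n is the sample size per group". Its inputs are "standard deviation of the primary outcome variable stress level of the mother as measured by serum cortisol level = 2.58 μg/dl" and "d = clinically significant difference = 0.55 μg/dl", a two-sided 5% level, 80% power and 10% attrition, giving 768. The SD is described as that of a cortisol level, not of a change or a residual. The section does not say at which sample the difference of 0.55 is expected.

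The Data analysis section assigns a different method to this variable: "A comparison of behavioural response and stress level of low-risk primigravid women among experimental and control groups will be done using repeated measures of ANOVA". It does not say whether the group main effect or the group-by-time interaction is the test of treatment.

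Cortisol is measured twice in each woman, the second time at full dilatation. The Abstract and the Outcome measures section put the first sample at 3–4 cm of dilatation. The section on serum and neonatal cortisol assessment puts it at 4–5 cm. The Intervention section has the ball in use at or after 4 cm. Randomisation is at 2–3 cm.

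**The concern.** The sample-size formula gives the power of one comparison: mean cortisol in one group against the other at a single time. A repeated-measures ANOVA on two samples offers two other tests. The group main effect compares the average of the two samples, so an effect that appears only at the second sample is halved. The group-by-time term with two time points is a t-test on the change, and its variance exceeds that of a single sample when the within-woman correlation is below 0.5. Neither test has the power that the formula describes, except by coincidence.

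At stake is whether the 80% stated for the variable that sizes the trial applies to the test that will be run. Efficiency also matters. A first sample taken before the intervention would be a useful covariate, and a repeated-measures ANOVA does not make the best use of it.

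**Working it through.** **Inputs.** From the Sample-size section: σ = 2.58, d = 0.55, z values "1.96 at α = 0.05" and 0.84 for 80% power, attrition 10%. Not in the protocol, so assumed: the correlation ρ between a woman's two samples (varied), equal variances at the two samples, and an effect of 0.55 at the second sample only.

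**1. Reproduce the plan's figure.** n = 2(1.96 + 0.84)² × 2.58² / 0.55² = 345.03 per group. 345.03 / 0.9 = 383.4, rounded up to 384; 2 × 384 = 768. The figure is correct for a two-sample comparison. It leaves about 345 completers per group (768 × 0.9 / 2 = 345.6).

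**2. Power of each candidate test.** Power = Φ(effect / SE − 1.96), with SE = SD × √(2/345) and √(2/345) = 0.0761.

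- Second sample only: effect 0.55, SD = σ.
- Group main effect: effect 0.55 / 2 = 0.275, SD = σ√((1 + ρ)/2).
- Group-by-time: effect 0.55, SD = σ√(2(1 − ρ)).
- ANCOVA on the first sample: effect 0.55, SD = σ√(1 − ρ²).

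Worked at ρ = 0.3:

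- Second sample only: SE = 0.196; 0.55 / 0.196 = 2.80; power 80%.
- Main effect: SD = 2.08, SE = 0.158; 0.275 / 0.158 = 1.74; power 41%.
- Group-by-time: SD = 3.05, SE = 0.232; 0.55 / 0.232 = 2.37; power 66%.
- ANCOVA: SD = 2.46, SE = 0.187; 0.55 / 0.187 = 2.94; power 84%.

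| ρ (assumed) | Group main effect | Group-by-time | Second sample only | ANCOVA |
|---|---|---|---|---|
| 0 | 51% | 51% | 80% | 80% |
| 0.3 | 41% | 66% | 80% | 84% |
| 0.5 | 37% | 80% | 80% | 90% |
| 0.7 | 33% | 95% | 80% | 98% |
| 0.9 | 30% | >99% | 80% | >99% |

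The main effect stays between 30% and 51%. The interaction reaches 80% only from ρ = 0.5 upwards. At ρ = 0.3 the interaction would need 345.03 × 2 × 0.7 = 483.05, so 484 per group; 484 / 0.9 = 537.8, so 538 per group, or 1,076 in total.

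**3. If the first sample is taken after the ball is in use.** Let the first sample already carry half of the effect (an assumption, f = 0.5). The estimated effects become 0.55(1 − ρf) for ANCOVA, 0.55(1 − f) for group-by-time and 0.55(1 + f)/2 for the main effect, with the same SDs.

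| ρ (assumed) | Group main effect | Group-by-time | Second sample only | ANCOVA |
|---|---|---|---|---|
| 0.3 | 74% | 22% | 80% | 70% |
| 0.5 | 68% | 29% | 80% | 68% |
| 0.7 | 62.5% | 44% | 80% | 72% |

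Here ANCOVA falls below the plain second-sample comparison, and at ρ = 0.3 below the main effect too. It also no longer estimates the full difference: at ρ = 0.5 it targets 0.55 × 0.75 = 0.41.

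**The case against.** **Repeated-measures ANOVA is valid, and the loss depends on an unknown.** It is a legitimate comparison of groups. With a pre-intervention first sample, its natural treatment test is group-by-time, which meets or exceeds 80% once ρ is 0.5 or more. The low main-effect figures apply only if that term is tested and the first sample carries no effect. All of this stands, so the mismatch does not always cost power. What remains is that the protocol gives neither ρ nor the tested term, so its 80% is not tied to the test it plans.

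**Naming the model term could be left to an analysis plan.** That is fair for the term alone. But the protocol itself states both the sizing formula and the method, and the two address different contrasts.

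**ANCOVA is not always best.** This stands. A reader of the first power table might conclude that ANCOVA wins in every case. The protocol's timings do not support that: a first sample at 4–5 cm, with the ball used from 4 cm, may be post-intervention, and the second table shows the consequence.

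**Two competing analyses?** A reader might also infer that cortisol has been given two rival tests, because the Outcome measures section lists it among the maternal outcomes and the Data analysis section says: "Two independent samples t-test/Mann-Whitney U-test (based on normality of data) will be used to determine the effectiveness of the usage of peanut ball". The documents do not bear this out. The Research objectives place stress level in objective 3, apart from the maternal outcomes of objective 1. The Hypotheses separate H1 from H3 in the same way. The Data analysis section says that it follows the objectives and hypotheses, and it names repeated-measures ANOVA for stress level specifically. The list under Outcome measures is a list of measurements, not an assignment of tests.

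**Conclusion.** The point holds in a conditional form. The figure of 768 is correct for the comparison it was computed for, but the analysis named for that variable is a different one. If the effect is at the second sample only, the planned model gives 30–51% power through the main effect over ρ = 0 to 0.9. Through the interaction it gives at least 80% only when ρ is 0.5 or more. ANCOVA on a genuine pre-intervention sample is never weaker than the interaction or the second-sample comparison, and it uses data already planned.

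This rests on an assumed ρ, equal variances, 345 women per group with both samples, and a first sample that precedes ball use. The last condition is unsettled in the protocol. If it fails, the advantage of ANCOVA is not assured: with half of the effect already in the first sample, its power is about 68–72%, below the 80% of the unadjusted comparison.

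**What to change.** - Name maternal serum cortisol at the second sample (full dilatation) as the primary cortisol contrast.
- Analyse it by ANCOVA on group with first-sample cortisol as covariate, and report the adjusted difference with its 95% CI. This replaces repeated-measures ANOVA for this endpoint.
- Fix the scale in advance, not from the trial data. The raw scale keeps the link to the SD of 2.58 and the difference of 0.55; a log scale would break it.
- Reconcile the two timings of the first sample (3–4 cm and 4–5 cm) with the start of ball use. If the first sample cannot be shown to precede ball use, use the unadjusted second-sample comparison. Make this choice once for the whole trial, before outcome data are analysed.
- Do not adjust for the clock time of the second sample. It arises after randomisation and depends on the duration of labour, which is itself an outcome. Induced versus spontaneous labour may be added only if it is fixed before randomisation.
- Keep 768. It matches the unadjusted comparison and is conservative for ANCOVA on a pre-intervention sample at any ρ above 0.

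The cost is a few sentences of analysis wording and the timing reconciliation; no new blood samples are needed. Because recruitment is under way, the sponsor must also establish when first samples were taken from women already enrolled. The article does not say whether that time relative to ball use is recorded.

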### Monitoring

Data monitoring committee will be formed, which includes methodology experts, subject experts and statistician.

### Ethics and dissemination

Approval has been obtained from Head of the Unit - Obstetrical and Gynecological department and Medical Superintendent Kasturba Hospital Manipal for this study. Ethical clearance for the study was obtained from the Kasturba Medical College and Kasturba Hospital, Institutional Ethics committee Manipal (Reg No: ECR/146/1nst/KA/2013/RR-16). The trial is registered under the Clinical Trial Registry of India (CTRI/2019/08/020802). A written participant information sheet (
[name], 2022b) will be given regarding the details of the study, and it will be explained to all low-risk primigravid women before enrolment to the study. Their involvement benefits and harm (none) as well as whom to contact in case of doubt will be explained to the participants. Written informed consent (
[name], 2022c) from the participants will be obtained before involving them in study.

### Confidentiality

Confidentiality of the research data collected will be maintained strictly as per the ethical standards. Only the research assistants and the researchers will have access to the participants’ data in the study. The data and results from this study may be presented at conferences and published in scientific journals without revealing the identity of the participants.

### Injury compensation

During the study period, if any medical problem arises as a direct result of the study intervention, the researchers will be responsible for ensuring proper medical care is provided to the participant. Suppose a participant suffers from any injury (physical/mental) or disease/illness as result of the correctly implemented study procedures. In that case, the researcher is responsible for that unless the injury or disease relates to the mothers negligent or reckless act.

### Dissemination plans

The time of sharing data is within one year after completion of the trial. The findings will be disseminated to participants, healthcare professionals, the public, and other relevant groups by attending scientific conferences and publishing in reputed journals.

## Discussion

Labor is a complex phenomenon in which the passenger (fetus) goes through the passage (pelvis) using the power (contractions) to deliver a healthy neonate (
Michelle & Gayle, 2020). In order to accelerate the labor a series of interventional strategies have been adopted, and one among them is use of peanut ball during labor. Utilisation of peanut ball has proven effective in reducing cesarean section rates, drop in the length of the first stage of labor by more than 90 minutes and the second stage was reduced by 22.3 minutes. Additionally, the need for vacuum extraction and forceps delivery is decreased in the group using the Peanut Ball. It also use of peanut ball helps in labor progress by easing labor pain and reducing the discomfort of contractions, which indirectly lowers anxiety and increases a mother's positive childbirth experiences (
Tussey CM, 2015). The patient satisfaction was also noted in a qualitative study, which is done among 200 mothers, the study found out that, 118 laboring women who used peanut ball during their labor gave positive feedback in support of use of the Peanut Ball. Positive comments included that the Peanut Ball provided comfort, facilitated the progress of labor, and helped with the position. And 71 % would recommend the use of the Peanut Ball to other mothers (
Payton, 2015).

Globally, the peanut balls are extensively utilised by midwives to deliver the women through vaginal mode, but in India it is underutilised. Jayasudha,
*et al*. in the year 2021, did the quasi-experimental study in India, in which peanut ball use during the first stage of labor is explored (
Jayasudha *et al.*, 2021). The study lacks a controlled setting; the stakeholders consider methodologically rigorous research evidence to make a decision related to policymaking. However, there is currently no proof that the peanut ball, used as a birthing ball, has any effect on women. The potential benefits of employing the peanut ball in India must be further investigated, especially given the current high rate of caesarean sections.

In the present study, a clinical trial with block randomisation to investigate the effectiveness of peanut ball in improving maternal and neonatal outcomes is planned in the Indian context to make the appropriate clinical decision. The effect of the peanut ball for labor among low-risk primigravid women in India will be the subject of a first-ever study.

For the study the participant recruitment began in the month February 2020. To date, we have enrolled and randomised 550 low-risk primigravid mothers. Out of the total, 225 mothers were recruited to the intervention and 225 mothers were recruited for the control group. Mothers’ unacceptance to utilise the peanut ball during labor is a challenge faced during the initial part of the study. To encounter this, all the primigravid women at or after 37 weeks of gestation attending antenatal outpatient units were given informational material about the “Peanut ball use during labor”. This educational material has oriented and familiarised the mothers with peanut ball and its uses during labor which ultimately increased the rate of peanut ball acceptance and use during labor.

Along with that, coronavirus disease 2019 (COVID-19) imposed a lockdown, and after that, institutional restrictions to resume research activities to mitigate new cases of infection had made the study come to a halt. Recruitment for the study was stopped, and we lost participants for around five months. Due to this situation, we have fallen behind the recruitment timeline. To combat this, we utilised this duration to initiate a systematic review that will bring new evidence to implement peanut ball during labor.

Besides these challenges, there are two possible limitations in this study, first, ascertainment bias, as the investigators are aware of the intervention the participants are receiving. In this project, the investigator and participants will know the allocation group for the women, as the woman will either utilise the peanut-ball or not, so they cannot be blinded. The strategy implemented to reduce the ascertainment bias is allocation concealment using SNOSEs by the labor room senior nurse on duty. The research assistant and research nurse carrying out data collection, data entry, and data analysis will be blinded to group allocation. The second limitation is compliance with the intervention during labor. To tackle this, a trained nurse will be present throughout the labor process and encourage and motivates the mothers to use the peanut ball continuously.

Despite these possible limitations, this novel approach will be a promising intervention to promote labor progress and prevent unnecessary caesarean section and instrumental birth during the second stage of labor.

## Conclusion

In this paper, researchers described the study design and the methodological approach adopted to evaluate the effectiveness of use of peanut ball during labor. Expected results of the study are usage of peanut ball helps in widening the pelvic outlet thereby supporting the natural progression of birth by increased maternal-fetal circulation, decreased pain and labor stress, and fewer abnormal fetal heart rate patterns, decreased duration of labor, less risk for postpartum hemorrhage and reduce the number of cesarean section rate. This project would thus enable to reduce maternal morbidity and mortality and can be used as a guide to implement peanut ball use in the labor rooms of tertiary health care settings in the Indian context and all over the world.

## Data availability

### Underlying data

No underlying data is associated with this article.

### Extended data

This project contains following extended data:

Figshare: Demographic proforma.docx.
https://doi.org/10.6084/m9.figshare.19122233 (
[name], 2022a)

Figshare: Participant Information Sheet.docx.
https://doi.org/10.6084/m9.figshare.19122230 (
[name], 2022b)

Figshare: 18 Informed Consent English.doc
https://doi.org/10.6084/m9.figshare.19122242 (
[name], 2022c)

Data are available under the terms of the
Creative Commons Zero “No rights reserved” data waiver (CC0 1.0 Public domain dedication).

Figshare: Screening Tool.docx.
https://doi.org/10.6084/m9.figshare.19122239 (
[name], 2022d)

Data are available under the terms of the
Creative Commons Attribution 4.0 International license (CC-BY 4.0).

Figshare: Tool III modified partograph.docx.
https://doi.org/10.6084/m9.figshare.19122236 (
[name], 2022e)

Data are available under the terms of the
Creative Commons Zero “No rights reserved” data waiver (CC0 1.0 Public domain dedication).

Figshare: Structured observational record on outcome of the labor.docx
https://doi.org/10.6084/m9.figshare.19122227 (
[name], 2022f)

Data are available under the terms of the
Creative Commons Attribution 4.0 International license (CC-BY 4.0).

## Reporting guidelines

Repository: SPIRIT checklist for ‘Effectiveness of a peanut ball device during labor on maternal and neonatal outcomes: protocol for a randomised controlled trial’.
https://figshare.com/s/5e8db2fc8dee7a7e06e5 (
[name], 2022g)

Data are available under the terms of the
Creative Commons Attribution 4.0 International license (CC-BY 4.0).
